### Recruitment

Procurement of subject lists was straightforward and timely, with exclusions readily identifiable from existing data fields (Figure 1). Six ineligible mothers were included in the trial as a result of recording errors in the data fields (e.g., mothers whose infants had had an extended Neonatal Intensive Care Unit (NICU) stay or mothers who were non-residents of SA). An additional five mothers included in the trial would have been excluded had it been possible to audit all the medical records prior to randomisation. Examples were mothers who were incarcerated, mentally incapacitated, or whose baby was placed into foster care. If the mother's exigent circumstances were discovered upon audit of the medical record (to follow-up returned mail or non-contacts for the telephone interview), no further contact was attempted.

### Implementation of telephone interviews

Households were initially contacted on the day the infant reached 10 weeks of age. A minimum of three calls was made at varying times of the day (morning, afternoon, evening) before a household was classified as non-contactable. Interview recruitment was high: 1026 parents were interviewed (91%), of whom 925 (82%) completed the interview and 101 (9%) partially completed the interview. A partially completed interview was usually one where the parent answered one question only: the reason why they did or did not return the reply form. There were 57 non-contactable households (5%) despite repeated attempts and a connected telephone number. A further 13 households (1%) were non-contactable due to disconnected or wrong telephone numbers recorded in the hospital system, while 28 (2%) were non-English speaking and 5 (< 1%) refused to be interviewed.

## Discussion

This is the first RCT of opt-in and opt-out parental consent for a population-based childhood vaccine safety surveillance program using data linkage. It featured a parallel design, adequate power for the primary outcome and thorough follow-up of subjects to determine attitudes to consent, data linkage and other important issues.

The comprehensive list of socio-demographic variables included in the hospital's patient management system provided basic information on a range of socio-demographics for all mothers: age, marital status, country of birth, Indigenous status, household location (major cities or other) and IRSD. It will, therefore, be possible to determine the presence of selection bias in the participation rate, irrespective of whether a subject answered the socio-demographic questions in the interview. The previous RCTs of opt-in versus opt-out consent [26-30] did not show such comparisons [26,27], or were restricted by the small number of socio-demographic characteristics for which data were available for all eligible patients: either age and sex alone (which gave no insight) [28,30], or age, sex and the IRSD (which gave limited insight) [29].

The recruitment rate for the interview was high for a number of reasons. Firstly, SA Health's data listings recorded a mother's mobile and landline telephone number and often a spouse or *de facto's *mobile number, enabling parents to be contacted even if they had changed residence. Secondly, the interviewers were persistent in the follow-up of returned mail and non-contacts for the interview, and optimised contact through auditing medical records to find valid residential addresses and telephone numbers. Thirdly, parents usually had a good rapport with the hospital as recent recipients of its health services and were willing to participate in the research for altruistic reasons.

This trial focused on parental attitudes towards using data linkage in one context: childhood vaccine safety surveillance. Although there will be some overlap in motivators and barriers to participation, some important determinants of participation among parents may not be relevant for data linkage studies in other health-related areas. The portfolio of evidence on the public's preferences for consent and attitudes towards the intrinsic value of data linkage, levels of trust in its protection of privacy in different population/patient groups and in different health areas requires expansion.

The cut-off time for data to be included in the estimation of the participation rate was chosen *a priori *to allow parents sufficient time to immunise their infants, and for adverse events to be captured, and to balance the potential for recall bias against potential for late returns. Every parent had four weeks to respond to the study invitation material and did not receive follow-up reminders. Based on findings from previous surveys [38,39], we anticipate that the number of parents who opted in or opted out may be half those attained if follow-up mailings had been implemented. We accepted reply forms that were received within a week of the interview at 10 weeks post-partum, which prompted a small number of crossovers. For example, a parent in the opt-in arm may have answered in the interview that they had been too busy to send back the reply form, but the process of being interviewed reminded them to do so. In this instance, it is unlikely the parent would have returned the reply form of their own volition.

The interviews may have been subject to respondent bias, in that parents may not have honestly reported motivations and barriers to the return or non-return of reply forms in a telephone conversation with a 'stranger' affiliated with the trial. While qualitative methodology may be more successful in revealing true motive, facilitated by developing rapport with interviewers and/or focus group members through in-depth exploration of reasons underlying participation and non-participation, fewer parents could have been studied in the same time.

We did not engage interpreter services for non-English speakers. While the number of parents who had no English comprehension was smaller than anticipated (2%), we encountered parents with varying levels of English proficiency, ranging from the ability to comprehend and answer a small number of questions in the interview (usually only questions related to vaccinations practices and episodes of infant illness) to answering all questions, but with some uncertainty as to their understanding. The interviewers flagged the interviews in which they perceived the parents' English to be limited, and this can be used as a covariate in the analysis, in addition to the socio-demographic variables that provide information on country of birth and main language spoken at home.

Informed consent is generally regarded as an essential component of health research. Low participation rates in health and medical research can lead to selection bias and compromise statistical precision. Therefore, consent procedures should aim to reduce bias and improve participation rates. VALiD is the first RCT to compare opt-in with opt-out parental consent for a population-based childhood vaccine safety surveillance program using data linkage. This study fills a gap in the literature in that it will not only assess the participation rate and selection bias for each consent option but, through a subsequent telephone interview of all households, will also assess consent preferences and intent compared with actual opting in and opting out behaviour, and socioeconomic factors. The findings will have relevance to all stakeholders and policy makers and will stimulate public debate about what it means to protect patients' interests.

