### Intervention and follow-up

All households received a cover letter (addressed to the mother), an information leaflet and a reply-paid form, with different formats according to allocation to the opt-in or the opt-out arm (Figure 1). The study material invited parents to be part of a 'Vaccine Data Linkage Study' in order to investigate data linkage as a new way of checking for rare reactions to vaccines by looking at large numbers of children. Parents were asked for permission to link infants' two-month vaccination records with any hospital visits occurring in the month following vaccinations. The study invitation was mailed after randomisation at six weeks post-partum; its arrival was timed to advise parents of the study one to two weeks prior to the scheduled two-month vaccinations. Parents in the opt-in arm were instructed to return a reply form to signal willingness to participate in data linkage; whereas parents in the opt-out arm were informed they would be included unless they returned a reply form to refuse consent. Telephone or email response was also accepted. No follow-up reminder letters were sent, to make the participation rate - the response to one invitation - relevant to large population data linkage studies. The cut-off time for data to be included in the estimation of the participation rate at 10 weeks post-partum included the first day of the 11th week to allow for internal hospital postal delays, giving all parents four weeks to respond. The telephone interview occurred when infants reached 10 weeks of age, corresponding with one to two weeks after administration of the two-month vaccinations to enable data collection on vaccination practice and experience of adverse events.

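### The primary outcome is meant to be the reply to one unreminded invitation, but forms prompted by the trial's own interview were accepted, and its cut-off date is not clearly fixed

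*Protocol article*

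**What the plan says.** All three places are in the protocol article.

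- **Intervention and follow-up** fixes the timing and the purpose of the outcome. On mailing: "The study invitation was mailed after randomisation at six weeks post-partum". On closing, the limit set at 10 weeks of age "included the first day of the 11th week to allow for internal hospital postal delays, giving all parents four weeks to respond". On purpose: "No follow-up reminder letters were sent, to make the participation rate - the response to one invitation - relevant", with population-scale linkage in mind.
- **Implementation of telephone interviews** starts the calls at the same age: "Households were initially contacted on the day the infant reached 10 weeks of age". At least three calls were made before a household counted as non-contactable, and 1026 of 1,129 households (91%) were interviewed.
- **Discussion**, in the paragraph on the participation-rate cut-off, repeats the window: "Every parent had four weeks to respond to the study invitation material and did not receive follow-up reminders". It then adds: "We accepted reply forms that were received within a week of the interview at 10 weeks post-partum, which prompted a small number of crossovers". Its example is an opt-in parent who had not found time to reply, was reminded by the interview, and would probably not have replied otherwise.

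The analysis plan gives no rule for responses received after the interview. The abstract says that analysis had not yet been undertaken.

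**The concern.** There are two problems. First, one section closes the outcome at an infant age tied to a four-week window, while the other accepts forms for a week after the interview. A household whose form arrives between the two limits may be a participant under one rule and a non-participant under the other.

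Second, whatever the exact date, the interview asks why the form was or was not returned, and the article accepts that this reminded some parents. Counting those forms brings a reminder into an outcome that was designed to have none.

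The effect differs by arm in a known way. A prompted return adds a participant in the opt-in arm and removes one in the opt-out arm, so equal prompting does not cancel. At stake are the primary difference, each arm's rate against the 90% threshold in the second primary hypothesis, and the consenting and non-consenting groups that the secondary hypotheses compare.

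**Working it through.** **Plan's own figure.** For 80% versus 70%, two-sided 5% and 80% power, the normal approximation gives 294 per arm, or 313 with continuity correction. The plan states 313, and 313 × 1.10 = 344.3, stated as 344. The sample size reproduces and is not in question.

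**Dates, taking birth as day 0.**
- Mailing at six weeks is day 42. Four weeks later is 42 + 28 = day 70.
- First interview call, at 10 weeks, is day 70.
- One week after an interview on day 70 is day 77, and later if the interview needed call-backs.
- Reading A: the first day of the 11th week is day 70 or 71. This fits four weeks from mailing. It ends about a week before the later limit, and a form posted because of the interview could not normally arrive in time. The reported crossovers would then mean that the later limit was used.
- Reading B: it is day 77. This equals a week after an interview on day 70, but not after a later one. It is also 77 − 42 = 35 days, or five weeks, from mailing.

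**Size.** The article does not count the prompted forms, so the rates below are assumptions. Let a and b be the shares of interviewed non-returners who are prompted in the opt-in and opt-out arms. Take the plan's 70% and 80%, 91% interviewed, and about 1,129 / 2 ≈ 565 per arm (the actual split is not given).

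- Opt-in observed = 0.70 + 0.30 × 0.91 × a = 0.70 + 0.273a
- Opt-out observed = 0.80 − 0.80 × 0.91 × b = 0.80 − 0.728b
- Prompted forms ≈ 565 × (0.273a + 0.728b)
- Power = Φ[(d − 1.96 × √(2p̄(1 − p̄)/n)) / √((p₁(1 − p₁) + p₂(1 − p₂))/n)], where d is the difference, p₁ and p₂ are the two arms' rates and p̄ is their mean

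| a | b | Opt-in | Opt-out | Difference (points) | Forms (approx.) | Power, n = 565 |
|---|---|---|---|---|---|---|
| 0 | 0 | 70.0% | 80.0% | 10.0 | 0 | 97% |
| 2% | 0 | 70.5% | 80.0% | 9.5 | 3 | 96% |
| 5% | 0 | 71.4% | 80.0% | 8.6 | 8 | 92% |
| 10% | 0 | 72.7% | 80.0% | 7.3 | 15 | 82% |
| 2% | 1% | 70.5% | 79.3% | 8.7 | 7 | 92% |
| 5% | 1% | 71.4% | 79.3% | 7.9 | 12 | 87% |
| 10% | 2% | 72.7% | 78.5% | 5.8 | 24 | 62% |

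Worked example for a = 5%, b = 1%: d = 0.79272 − 0.71365 = 0.07907 and p̄ = 0.7532. The null standard error is 0.02565 and the alternative standard error is 0.02554. Then (0.07907 − 1.96 × 0.02565) / 0.02554 ≈ 1.13, which gives 87%.

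Per form: 1 / 565 = 0.18 percentage points of its arm.

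**The case against.** The strongest reply is that the two passages may state one rule. If 10 weeks post-partum covers days 70 to 76, the 11th week opens on day 77, exactly a week after an interview on day 70. The four weeks could run from arrival instead of mailing. The leaflet was timed for one to two weeks before the two-month vaccinations, and the 10-week interview for one to two weeks after them. That puts arrival at about 6 to 8 weeks, and four weeks from week 7 is day 77. This stands as a possible reading, so a flat contradiction, which a reader might infer, is not proven. The reading does not settle households interviewed after day 70.

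A reader might also infer that late contacts were given more time and non-contacts none. No passage says so. The Discussion refers to the interview at 10 weeks, which may be a nominal date.

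The crossovers are openly reported as few, within a cut-off chosen in advance, and the only example is from the opt-in arm. Prompted opt-out refusals are therefore an assumption. With opt-in prompting alone, every scenario above keeps power over 80%. Where opt-out is higher, the bias is also conservative and cannot create an apparent opt-out advantage. All of this limits the size. Disclosure does not remove the bias, though, and a conservative test still gives a shifted estimate of each rate.

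**Conclusion.** The point holds as a problem of outcome definition. The article intends a reply to one unreminded mailing, yet accepts forms that it says its own interview prompted, and it does not clearly give one closing date. The direction of the bias is towards zero, provided that opt-out exceeds opt-in, as the sample-size section assumes. The opt-in rate can only move up and the opt-out rate only down, which also matters for the comparison with 90%.

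The size is probably modest: 0.18 points per form, and a difference of 7.9 to 8.7 points instead of 10 for about 7 to 12 forms, with power of 87% to 92%. A serious loss of power might be inferred, but the documents do not support it. Power of 62% needs about 24 forms, which sits poorly with a small number. Power of 75%, 67% and 43% for the three two-arm scenarios arises only at the planned 344 per arm, and 1,129 households were recruited.

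Two assumptions remain. That these forms enter the primary outcome is inferred from their acceptance and the mention of crossovers in the cut-off paragraph; if they do not enter it, the text should say so. The prompting rates are illustrative.

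**What to change.** Before analysis, state one closing date as an infant age in days. For the primary analysis, classify each household by responses of any kind (form, telephone or email) received up to that date and before its telephone interview. A response first received after the interview does not change the household's status. Households never interviewed are classified at the closing date alone.

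Report the rule that accepts forms within a week of the interview as a sensitivity analysis, with the number of post-interview responses in each arm.

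The cost is a sentence in the outcome definition and the recoding of a small number of households, provided that receipt and interview dates were kept. A few genuine forms already in the post at the interview would move to the sensitivity analysis. Form dates or postmarks could rescue them, but only if these were recorded, which the article does not say.

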## Abbreviations

CYWHS: Children, Youth and Women's Health Service; HREC: Human Research Ethics Committee; IRSD: Index of Relative Socio-Economic Disadvantage; NICU: Neonatal Intensive Care Unit; RCT: Randomised controlled trial; SA: South Australia; SEIFA: Socio-Economic Indexes For Areas; VALiD: Vaccine Assessment using Linked Data; WCH: Women's and Children's Hospital; UK: United Kingdom of Great Britain and Northern Ireland; US: United States of America.

